**Effect evaluation: primary outcome**				
a. Sense of competence	SCQ [45]	X	X	X
**Effect evaluation: secondary outcomes**				
b. Quality of life of the caregiver	SF-36 [48]	X	X	X
	EQ 5-D [57]	X	X	X
c. Psychological well-being of the caregiver	CES-D [49]	X	X	X
d. Caregiver's burden	SPPIC [50]	X	X	X
e. Days until institutionalization of the patient	GP	continuous registration		
f. Quality of life of the patient	DQOL [51]	X	X	X
	EQ 5-D [57]	X	X	X
g. Days until death of the patient	GP	continuous registration		
h. Hospital days of the patient	Cost diaries	continuous registration		
**Economic evaluation**				
i. Direct and indirect costs	Cost diaries and home-care organisation	continuous registration		

#### Effect evaluation

Primary outcome is:

1. Caregiver's sense of competence as measured with the Sense of Competence Questionnaire (SCQ) [45].

The SCQ consists of three domains, identified by factor analysis: consequences of involvement in care for the personal life of the caregiver, satisfaction with one's own performance as a caregiver and satisfaction with the impaired person as a recipient of care. The questionnaire was based on Zarit's Burden Inventory [46] and Bengtson and Kuypers' family crisis model [47].

Secondary outcomes are:

2. Caregiver's quality of life by means of the MOS 36-item short-form health survey (SF-36) [48];

3. Caregiver's psychological well-being as determined with the Center for Epidemiologic Studies Depression Scale (CES-D) [49];

4. Caregiver's burden by means of the Self-Perceived Pressure by Informal Care (SPPIC) [50];

5. Days until institutionalization of the patient as checked with GP records;

6. Patient's quality of life as measured with the Dementia Quality of Life Instrument (DQOL) [51];

7. Days until death of the patient as checked with GP records;

8. Hospital days of the patient by means of cost diaries.

Apart from these outcomes, we assess the following potential confounding variables on the level of the caregiver: socio-demographic characteristics, disabilities in activities of daily living (ADL) functioning and instrumental activities of daily living (IADL) functioning by means of the Groningen Activity Restriction Scale (GARS) [52], presence of chronic diseases, locus of control (Mastery) [53], and social support (social support list) [54]. On patient level we assess socio-demographic characteristics, cognitive functioning (MMSE, 7MS, IQCODE), presence of chronic diseases, ADL and IADL disability with the Interview for Deterioration in Daily living activities in Dementia (IDDD) [55], behavioral problems and mood by means of the Neuropsychiatric Inventory (NPI-Q) [56], and incontinence.

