### Participants

Detection of patients and subsequent recruitment of their informal caregivers takes place among GP patients in West-Friesland, the Netherlands. Patients are potentially eligible for trial entry ifthey are 65 years or over, live outside of institutional settings, and suffer from dementia symptoms. Patients with dementia symptoms have multiple cognitive impairments (i.e. memory impairments, aphasia, apraxia, agnosia, and impairment in executive functioning). These symptoms lead to significant limitations in social functioning and progressive decline in general functioning. Two sources are used to detect patients; 1) Caseload of co-operating GPs. 2) The primary care Diabetic Research Center in which all GPs of West-Friesland participate. Detection of patients takes place in four ways, as shown in Figure 2. 1) GPs who are willing to co-operate, provide a list of addresses of all their patients, aged 75 or over and living at home. All patients receive a postal health questionnaire in order to identify older adults with cognitive decline, as assessed with a self-report version of the short Informant Questionnaire on Cognitive Decline (IQCODE) [36]. 2) Co-operating GPs mark patients who they suspect of dementia on the list of addresses they provide. 3) All GPs in West-Friesland invite patients suspected of dementia after consultation, for a cognitive assessment. 4) The primary care Diabetic Research Center provides addresses of their community-dwelling diabetic patients aged 65 or over and not approached formerly. Older patients with diabetes mellitus are more at risk of dementia and cognitive decline than those with normal glucose tolerance [37]. Diabetic patients also receive an IQCODE.

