### Intervention

During one year, three district nurses who are specialized in geriatric care, act as case-manager of both patient and informal caregiver. Case-management entails assessment, planning, coordination, collaboration, and monitoring of care. Nurses provide practical, informational and socio-emotional support. Multiple support strategies (e.g. support groups, respite care) are offered to informal caregivers and patients. The nurses start the intervention with a home-visit in which they administer a patient assessment; the Resident Assessment Instrument Home Care (RAI-HC). The RAI-HC is a computerized multidimensional instrument that consists of a Minimum Data Set (MDS) that assesses general functioning of the patient, and Client Assessment Protocols (CAPS), providing protocols for the management of 30 potential and actual problem areas [40]. Together with the participants, the nurses order the identified problems of the RAI into a hierarchy, and formulate a care-plan for these problems. Subsequently, they leave behind a form to register care received and appointments with health professionals. In the second home-visit, nurses explore the caregiver's situation with a capacity and burden questionnaire [41] and hand a guide to caregivers holding available social services and welfare professionals. The nurses formulate a care plan for the informal caregiver based on the capacity and burden questionnaire. After these two visits, the nurses and participants decide how they want to proceed with the intervention. When more visits are not necessary, the nurses contact the participants at least every 3 months to monitor their situation. The nurses leave a dossier at the patient's house. This dossier contains the care plan, identified problems by RAI assessment and notes of planned and undertaken activities. Other visiting health professionals may take notice of the dossier and add their own notes. The nurses contact the GPs to inform them about the situation. Apart from these compulsory activities, the intervention holds some tailor-made activities. When necessary, nurses refer to other health professionals, including diagnostic services and monitor the anticipated effect. In addition, the nurses may organize family-meetings to educate relatives, improve social support and relieve the caregiver [4]. Nurses were trained in working with the computerized RAI-HC, and in organizing family-meetings. They also received seminars on how to deal with dementia patients and their patients. They meet monthly to discuss innovations and geriatric cases while supervised by a staff member. Nurses provide care according to a National Guideline on dementia for district nurses [42].

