
### Usual care

Patients and informal caregivers in the control group receive usual care. In the Netherlands, all people are registered in a primary care practice. General practitioners, as well as a regional indication institution act as gatekeepers of the Dutch health care system. GPs provide cure according to the Guideline on dementia of the Dutch College of General Practitioners. They aim to diagnose and inform dementia patients and their relatives preferably at an early stage [43]. However, guideline recommendations in general, are followed in on average 67% of the decisions [44]. Co-operating GPs are unaware of patients allocated to usual care, unless participants reveal their allocation. Participants of the usual care group have no access to most of the structured and tailor-made activities of the intervention (e.g. family meetings, RAI-HC assessment, guide for informal caregivers). In the region of research, suspected patients are referred to mental health professionals, never to district nurses. All participants of the usual care group are offered the intervention after the one-year follow-up.

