### Blinding

Interviewers are kept blind from the randomization status of participants. GPs can be unaware of patients allocated to the usual care group, but they will be aware of patients in the intervention group as nurses contact the GP about these patients. Participants are not blinded.

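### Days until institutionalization is dated from GP records alone, and the intervention itself feeds information to GPs in one arm only, so recording could differ by arm

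*Protocol article*

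**What the plan says.** - **Source of the date.** The list of secondary outcomes under Effect evaluation gives "Days until institutionalization of the patient as checked with GP records". In Table 1 the row "e. Days until institutionalization of the patient" has the GP as its only instrument, under continuous registration. Table 1 does name two sources where two are used: the cost row lists diaries and the home-care organisation.
- **Information reaching the GP.** The Intervention section states that "The nurses contact the GPs to inform them about the situation", and the text that follows classes this among the compulsory nurse activities. The Blinding section says of GPs that "they will be aware of patients in the intervention group as nurses contact the GP about these patients". The Usual care section describes no matching contact.
- **Analysis.** Time to institutionalization is compared between arms with a Cox model (Analysis, Effect evaluation).
- **Contact that does not pass through the GP.** Trained interviewers, blind to allocation, visit at baseline, 6 and 12 months (Measurements; Blinding). They are not named as a source for this outcome.

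**The concern.** An event date should be collected in the same way in both arms. Here the recorder of the event is the GP, and the intervention includes a compulsory flow of information to that GP. If a case-managed patient moves to an institution, the nurse is a second route by which the GP may learn of it, and learn of it promptly. The article describes no such route for usual care.

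A placement that never reaches the record is analysed as a patient still at home, and one recorded late adds days at home that did not occur. If either happens more often in usual care, case-management appears to hasten institutionalization. Randomization in blocks within practice does not remove this, because the difference arises between patients of the same practice.

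At stake is the institutionalization part of the secondary research question. The primary outcome is a caregiver questionnaire that does not depend on GP records.

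**Working it through.** **What the plan gives.** There is no event count, hazard ratio, power or placement rate for this outcome. The only sizing figure is for sense of competence: 37 per group with 25% drop-out. That is 37 / 0.75 = 49.3, rounded up to 50 per group, or 100 in total as stated. I use 50 per arm below.

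**Assumptions, none of them from the article.** True hazard ratio 1; the same one-year placement risk p in both arms; full capture in GP records under case-management; a fraction c captured in usual care; constant hazards; no drop-out.

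**Formula.** Apparent HR (case-management vs usual care) = ln(1 − p) / ln(1 − p·c).

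- p = 0.20, c = 0.90: ln(0.80) / ln(0.82) = 1.12
- p = 0.20, c = 0.80: ln(0.80) / ln(0.84) = 1.28
- p = 0.30, c = 0.80: ln(0.70) / ln(0.76) = 1.30
- 80% capture in both arms: numerator and denominator are equal, so HR = 1.0

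**Range for p from 10% to 40%.**

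| Capture in usual care | Apparent HR |
|---|---|
| 100% | 1.0 |
| 90% | 1.12 to 1.14 |
| 80% | 1.26 to 1.32 |
| 70% | 1.45 to 1.56 |

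**Late recording.** This was simulated with 4,000 trials per setting, 50 per arm, exponential times, follow-up to 365 days and a nominal two-sided 5% log-rank test. With complete and prompt records the test rejected in 4.7% to 4.9% of trials.

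| Usual-care recording | p | Median HR | Rejection rate |
|---|---|---|---|
| Mean delay 60 days, all captured | 20% / 30% / 40% | 1.22 / 1.24 / 1.25 | 7.4% / 8.5% / 10.2% |
| 80% captured, no delay | 20% / 30% / 40% | 1.28 / 1.30 / 1.33 | 8.1% / 10.2% / 13.2% |
| 80% captured, mean delay 60 days | 20% / 30% / 40% | 1.52 / 1.60 / 1.62 | 13.8% / 21.5% / 29.3% |

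**Scale.** At p = 0.20 with 50 per arm, 90% capture means 10 recorded events against 9, a difference of one placement. The approximate 95% interval around 1.12 is 1.12 × exp(±1.96 × √(1/10 + 1/9)), or 0.46 to 2.8. For 80% power the detectable HR is exp(2.80 / √(D/4)): about 3.5 with D = 20 events and 2.4 with D = 40. The modest distortions in the first table are therefore small beside the sampling error of this comparison.

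**The case against.** Several arguments on the other side carry weight.

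- **The asymmetry does not prove under-recording.** A GP keeps the record for clinical care, whatever contact a nurse makes. The Discussion also expects that GPs may be prompted to give usual-care patients more attention, which would narrow any gap. This stands: the article documents a mechanism, not its effect, so placements in usual care *could* be missed or dated later.
- **The article is condensed.** A cross-check may be described in the full protocol. This stands as a limit. Still, Table 1 lists a second source elsewhere, and none is named here.
- **GP records are a reasonable source.** They can still be consulted for the roughly 25% expected to drop out, whereas caregivers are unblinded and may misremember dates. This stands, and is why GP records should be kept.

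A reader might also infer more than the text supports:

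- **GPs do not know about usual-care patients.** The article says "Co-operating GPs are unaware of patients allocated to usual care, unless participants reveal their allocation". That concerns allocation, not whether a GP knows that a registered patient has moved.
- **A second gatekeeper means missed placements.** The article says "General practitioners, as well as a regional indication institution act as gatekeepers of the Dutch health care system". This makes an incomplete GP record plausible, but it applies to both arms and creates no difference without the one-sided nurse contact.
- **GPs who do not co-operate leave gaps.** The text is "GPs who are willing to co-operate, provide a list of addresses of all their patients, aged 75 or over and living at home". Co-operation here concerns address lists for case detection, not access to outcome records. Everyone is registered with a practice, and blocking by practice balances practices across arms.
- **The date of death needs a new source too.** It also comes from GP records, but the article shows no separate defect there, and the point does not extend to it.

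**Conclusion.** The point holds as a risk of differential ascertainment for one secondary outcome. It rests on two statements in the article: GP records are the only named source, and nurse-to-GP contact belongs to one arm only. If recording does differ, the likely direction is against case-management.

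The size cannot be established. The hazard ratios of 1.12 and 1.28 depend on an assumed 20% risk and full capture under case-management, and they fall to 1.0 if capture is equal. They do not show that the trial's hazard ratio is biased. The matter deserves correction because the safeguard is cheap and the visits already take place; conclusions on the primary outcome do not depend on it.

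**What to change.** At the 6- and 12-month visits, after the outcome scales, the blinded interviewer asks the caregiver in both arms where the patient lives and, if there has been a permanent move, its date. Combine this with GP records, which remain the source for pairs lost to follow-up. Resolve conflicting dates without knowledge of arm, and report agreement between the two sources by arm, so that a reader can see whether GP recording differed.

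The cost is a short extra question at visits already planned and a reconciliation step. Caregiver dates will carry some recall error over six months and come from unblinded respondents, so they should complement GP records, not replace them.

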**Methods/design:**

In this randomized controlled trial, effectiveness as well as cost-effectiveness of case-management is evaluated. It concerns case-management in early-detected patients with dementia symptoms and their primary informal caregivers. Participants are followed up to twelve months after baseline assessment. The main outcome measure of the effect evaluation is the caregiver's sense of competence to care for the older person with dementia symptoms. The economic evaluation is performed from a societal perspective.

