An innovative initiative to support dementia patients and their caregivers was set up by the Department of General Practice of the VU University medical center, GPs and district nurses in West-Friesland, the Netherlands. We developed a pro-active program, in which the key elements consist of timely detection of dementia symptoms followed by case-management by district nurses among detected patients and their primary informal caregivers. A randomized controlled trial (RCT) is performed to observe effectiveness and cost-effectiveness of case-management.

The objective of this paper was to describe the study protocol of this RCT among informal caregivers of men and women aged 65 years or over with dementia symptoms who live at home, and the men and women they take care of. The main research questions of this RCT concern whether case-management is more effective than usual care in improving caregiver's sense of competence, and whether case-management is cost-effective compared to usual care when assessed from a societal perspective. A secondary research question is whether case-management is more effective than usual care in improving caregiver's quality of life, caregiver's psychological well-being, caregiver's burden, patient's quality of life, and in decreasing hospital days, days until institutionalization and death of the patients.

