### Measurements

Table 1 provides an overview of all effect and economic measurements. At baseline (T0), and after 6 (T1) and 12 months (T2) trained interviewers visit participants. At baseline and after 6 months, they leave cost diaries for patients and caregivers to register medical consumption during the successive 6 months. These cost diaries also provide the possibility to visualize delivery of the intervention and usual care. When patients are unable to fill out a questionnaire, their informal caregiver is allowed to fill it out or to provide assistance.

**Table 1 T1:** Measurement Scheme

**variable**	**Instrument**	**T0**	**T1**	**T2**

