### Sample size calculation

Sample size calculations were based on scores reported for groups similarly to our target group on the main outcome measure of the RCT, namely sense of competence (mean 17.9 SD 5.2, range 4–27) [60]. Calculations are based on α = 0.05 and a desired power of 0.80. For an anticipated effect of 15% difference in final scores between intervention group and usual care group, and with improved scores in the intervention group and stable scores in the control group, 37 persons per group are required. As we expect a drop out rate of about 25% during the one-year follow-up, this means a total of 100 patients and caregivers to be included in the study.

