### Analysis

#### Effect evaluation

Data are primary analyzed according to the intention-to-treat principle. Additionally, data are analyzed according to the on-treatment (i.e. per protocol) principle in order to examine whether protocol deviations have caused bias. General Linear Models are used to analyze differences between the intervention and usual care group on caregiver's sense of competence, caregiver's quality of life and caregiver's psychological well-being. Potential baseline differences are accounted for by covariates. Differences in days until institutionalization and death between patients of the two groups are tested with survival analyses (Cox-proportional hazard modeling). Differences on patient's hospitalization days and patient's quality of life are tested by a chi-square test and student t-test, respectively. Potential confounding is checked, including the effect of different interviewers and nurses.

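### Hospital days are tested by chi-square with no link to time alive and under observation, so unequal death or drop-out between arms can produce an apparent difference

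*Protocol article*

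**What the plan says.** All places are in the protocol article.

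- **Research question (Background).** Case-management is to be more effective than usual care "in decreasing hospital days, days until institutionalization and death of the patients". Fewer hospital days are therefore read as benefit.
- **Outcome (Measurements, Effect evaluation).** The last of seven secondary outcomes is "Hospital days of the patient by means of cost diaries". Table 1 also gives the diaries as the source. No denominator or observation period per patient is attached.
- **Data collection (Measurements).** At baseline and at 6 months the interviewers visit, and "they leave cost diaries for patients and caregivers to register medical consumption during the successive 6 months". The Abstract states that "Participants are followed up to twelve months after baseline assessment".
- **Test (Analysis, Effect evaluation).** "Differences on patient's hospitalization days and patient's quality of life are tested by a chi-square test and student t-test, respectively". In the same paragraph, death and institutionalization get Cox models, which do use each patient's time at risk.
- **Loss (Sample size calculation).** "we expect a drop out rate of about 25% during the one-year follow-up". The Discussion adds that drop-out may be selective and names severely burdened caregivers and severely disabled patients. Its countermeasures are a fixed interviewer and convenient appointments.

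**The concern.** A patient can accrue hospital days only while alive, and these are recorded only while someone fills in the diary. Death and drop-out both shorten that time. A chi-square test, whether it compares any admission with none or categories of days, has no place for time at risk. A short record with few days then counts the same as a full year with few days.

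The arms could differ in observed time for reasons within the design. Death is an outcome that case-management is hoped to influence. Intervention families hear from a nurse at least every 3 months, controls are offered the programme only after a year, and participants are not blinded. Retention could differ in either direction. At stake is the reading of a named secondary outcome: an arm with more deaths or more drop-out could be credited with less hospital use, and an arm that keeps patients alive and in the study could be penalised.

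**Working it through.** **The plan's own figures.** No rate, variance or effect size is given for hospital days, so there is no figure for this outcome to reproduce. The one relevant number is the drop-out allowance: 37 / (1 − 0.25) = 49.3, rounded up to 50 per group, 100 in total, as stated.

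**Assumptions, not in the document.** Loss by arm; losses spread evenly over the year; days in partial diaries counted up to the point of loss; the same true rate of hospital days in both arms, here 8 per person-year; for the yes/no reading, the same admission hazard λ, here 0.5 per year.

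**Formulas.** With loss fraction d:

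- mean observed time = (1 − d) × 1 + d × ½ = 1 − d/2
- expected recorded days = rate × (1 − d/2)
- ratio of arm B to arm A = (1 − d_B/2) / (1 − d_A/2), whatever the rate
- proportion with any admission = (1 − d)(1 − e^−λ) + d[1 − (1 − e^−λ)/λ]; at λ = 0.5 this is 0.3935(1 − d) + 0.2131d

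| Loss, A v B | Observed years, A v B | Ratio B/A | Days at rate 8, A v B | Any admission, A v B |
|---|---|---|---|---|
| 25% v 25% | 0.875 v 0.875 | 1.000 | 7.0 v 7.0 | 34.8% v 34.8% |
| 20% v 30% | 0.900 v 0.850 | 0.944 | 7.2 v 6.8 | 35.7% v 33.9% |
| 15% v 35% | 0.925 v 0.825 | 0.892 | 7.4 v 6.6 | 36.6% v 33.0% |
| 10% v 40% | 0.950 v 0.800 | 0.842 | 7.6 v 6.4 | 37.5% v 32.1% |

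All the last three rows average 25% loss. At rates of 4 or 12 days per person-year the ratios are unchanged; the difference at 20% v 30% is then 0.2 or 0.6 day instead of 0.4. Days divided by observed time give a ratio of 1.00 in every row. From deaths alone, 10% v 20% gives 0.90 / 0.95 = 0.947, about 5%.

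**How likely is unequal loss?** Take 50 per arm and the same true 25% loss in both. The difference in number lost has variance 2 × 50 × 0.25 × 0.75 = 18.75, SD 4.33. The chance of a gap of 5 or more patients (10 percentage points) is about P(|Z| ≥ 4.5/4.33 = 1.04), or 30%. Chance gaps average out over repeated trials, so they are not bias in that sense, but they still distort the one comparison that is reported.

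A gap of 15% v 35% would need more than chance: SE = √(0.25 × 0.75 × 2/50) = 0.0866, z = 0.20/0.0866 = 2.3. For 10% v 40%, z = 0.30/0.0866 = 3.5.

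**The case against.** **This is detail for an analysis plan.** A condensed article need not describe offsets or truncation by death. That would settle it if the article were silent. But it names the outcome and fixes the test, and that test cannot use observed time, while the two neighbouring outcomes get a method that does.

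**The drop-out mechanism is assumed.** The article does not say how a drop-out's diary is scored. If patients without a returned diary are left out or imputed, the loss acts as missing data and the bias need not take the form shown. This stands, and it is why the figures are only illustrative. It does not remove the effect of death, after which no days can accrue.

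**The larger scenarios are extreme.** Gaps of 15% v 35% or more would be conspicuous in any report. The milder case gives about 6%, or 0.4 day at the assumed rate of 8. This also stands.

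**Total days over 12 months, with death reported beside it, is a recognised quantity.** True, but a lower total is then not a benefit by itself, which is how the research question reads it.

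Three stronger readings are tempting and are not supported:

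- A reader might infer that the plan compares raw totals. It does not say so; chi-square suggests proportions or categories.
- A reader might infer that institutionalization ends observation. It is an exclusion criterion at baseline only, and nothing stops visits or diaries when it occurs later.
- A reader might carry the point over to hospital costs. Costs accrued up to death are a legitimate quantity in an economic evaluation, and the QALYs there already multiply utility by time.

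**Conclusion.** The point holds in a limited form. The stated test for hospital days takes no account of time alive and under observation, in a one-year trial that expects about 25% loss, admits that loss may be selective and counts death as an outcome. If observed time differs between arms, the arm with less can show fewer hospital days with no true difference in rate. The direction is the same whether the test compares any admission or amounts of stay.

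The distortion is zero with equal observed time, about 6% at 20% v 30% loss, and about 11% at 15% v 35%. These figures rest on assumed loss by arm, uniform timing and partial diaries being counted. It would be too strong to say that the result will be biased or will point the wrong way: the document does not show that observed time will differ. The point touches one of seven secondary outcomes and leaves the primary outcome untouched.

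**What to change.** In Analysis, Effect evaluation:

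1. Replace the chi-square test for hospital days by a count model, for example negative binomial, with log(days alive and under diary observation) as offset. End observed time at the death date from GP records or at the last completed diary, whichever comes first.
2. Report deaths, observed time and the number of patients with no returned diary by arm. Patients with no returned diary have no exposure and drop out of the model, so their number must be visible.
3. Add days alive and out of hospital over 365 days as a supporting analysis, so that early death cannot score as benefit. State how days without a diary are handled for patients who drop out alive.

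The cost is a change of wording. Days until death are already taken from GP records, and diary periods follow from the baseline and 6-month visits. The downside is that the rate is conditional on being alive and observed, and the offset does not cure informative loss: if sicker patients leave earlier, their unrecorded days stay unrecorded. Items 2 and 3 limit that weakness but do not remove it.
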